
**Fig. 2 Fig2:**
[figure not shown]
Stepped Wedge Design. Pre: Pre-implementation; Impl: Implementation; Post: Post-Implementation; M: Maintenance

### Study design

The centerpiece of our study is a 12-site cluster-randomized stepped wedge trial evaluating the impact of the implementation strategies on the implementation of the care pathway, as well as the effectiveness of care pathway “bundle” implementation on effectiveness outcomes. Each site was considered a “participant.” The cluster-randomized stepped wedge trial design involves random and sequential crossover of clusters comprising three sites apiece from usual care to implementation until all sites receive the intervention. This design allows each site to serve as its own control. We can use this design to assess intervention effects and distinguish them from temporal trends. Continuous recruitment with short exposure minimizes patient exposure to both intervention and control conditions.

### Site eligibility and recruitment

The study will be conducted across 12 centers participating in the MEDIC program [16, 17]. MEDIC comprises over 50 hospital emergency departments, collectively processing more than 2 million visits annually, involving over 1200 emergency physicians. The MEDIC registry records data from over 2500 patients with acute pulmonary embolism (PE) each year. These sites encompass a mix of urban and non-urban, as well as academic and community settings, with more than half serving patient populations with over 20% non-white demographics, facilitating the study of implementation disparities.

A subset of MEDIC sites were identified as eligible for participation in this trial. Specifically, sites were considered eligible to participate if:They had an active MEDIC clinical champion who could facilitate implementation activities;They had an acute PE volume of ≥ 80 diagnoses in the 2022 calendar year.

All eligible sites were contacted by one of the study leaders ([name]), an ED clinician, to confirm eligibility and interest in study participation. Most sites were contacted through their existing MEDIC clinical champion by phone or email between January and May 2023. Of the 15 total sites that were contacted, 12 agreed to participate.

### Implementation mapping

Randomized sites in each step will proceed through several implementation phases. During the first phase, pre-implementation (three months), the study team will work with each site’s CQI Champion to designate a project leader (anticipated to most often be the current CQI Champion) and relevant stakeholders (e.g., pharmacists, social workers, administrators, information technology experts) who will also comprise the stakeholder coalition supporting implementation. The project leader and key stakeholders will then be tasked with tailoring both the care pathway components and study-provided implementation strategies to the local site needs. To inform this tailoring, the study team will conduct a needs assessment via semi-structured qualitative interviews with the identified stakeholders. Data from these interviews will be used to develop site-specific implementation mapping, specifically by updating the list of previously established determinants, identifying and/or tailoring specific care pathway components (e.g., identify entity responsible for rapid follow-up, tailor nudge modality), and assessing the feasibility of planned implementation strategies and, if needed, adapting specification (e.g., dosage or timing of coaching, modality of educational modules).

All identified stakeholders or other site decision-makers will be contacted by email and/or phone to complete an interview with the study team. To update implementation materials in a timely fashion, rapid qualitative inquiry will be used to identify new barriers and update the site-specific mapping of strategies to barriers. Reports on identified barriers/facilitators and planned implementation activities will be shared with each site. The FRAME and FRAME-IS frameworks [18, 19] will also be used to document modifications, including initial planned modifications to centrally provided implementation support.

### Evaluation of implementation and effectiveness outcomes

The full trial will roll out implementation support to 12 sites in four site groups, with each site advancing through four study phases (Fig. 2). As described above, the initial *pre-implementation phase* will focus on assessing site needs, identifying stakeholders, and tailoring the care pathway bundle to site needs. During the second phase, *implementation*, we will support sites in implementing the care pathway bundle, including implementing the site-provided implementation strategies specified in Fig. 2. The goal of this six-month phase is for sites to be ready to “go live” with the care pathway prior to phase end. This phase also comprises the most intensive study team-provided implementation support, including delivery of educational modules to care teams towards the end of this phase. The third study phase is *post-implementation*, which will last 12 months. During this phase, sites will continue to receive some support from the study team, but the expectation is that the care pathway “bundle” has been implemented and providers are beginning to utilize it. Sites will also begin to receive data audits from the study team during this time, showing their rates of PE discharge and change over time. Finally, the fourth phase will assess the *maintenance* of care pathway implementation and use. Given staggered study entry, time in this phase will range from three months (Group 4) to 12 months (Group 1).

A Data Safety and Monitoring Board will be comprised of three members who are free from competing interests and the sponsor, who report to the institutional review board with any findings of concern.

#### Randomization

Given interdependencies between certain sites (e.g., part of the same health system, use of a single EHR), it was not feasible to randomly assign individual sites to steps, as is best practice in stepped wedge designs. To maximize independence between clusters but accommodate these interdependencies, we created four groups of three sites each (e.g., three sites belonging to the same health system) and then randomized the order in which groups would begin rollout. This pragmatic design strategy also meant that we were not able to stratify rollout based on key baseline data (e.g., ED volume of low-risk PE patients).

## Measures and outcomes

### Outcomes

The RE-AIM implementation evaluation framework guided outcome selection [9].

### Adoption (primary outcome)

Our primary outcome will measure the change in the proportion of all acute PE patients discharged from the ED without hospitalization post-implementation vs. pre-implementation.

### Reach (secondary outcome)

For reach, we will examine the change in the proportion of patients with acute PE who qualify as low-risk (defined as Pulmonary Embolism Severity Index class I or II [20]) that were discharged post-implementation vs. pre-implementation. We will also examine demographic and comorbidity characteristics of the discharged patients (vs. not) to assess whether reach of the care pathway was equitable or whether it introduced or exacerbated disparities in care.

### Implementation Fidelity (secondary outcome)

Fidelity will be defined as implementation of the care bundle pathway components, including the site-provided implementation strategies, as planned. As noted above, FRAME [18] and FRAME-IS [19] will be used to document planned and ad hoc modifications to both the care pathway and implementation strategies (either site or study team-delivered). We will also quantitatively assess the level of implementation fidelity to the five care pathway “bundle” components described above: (1) rapid follow up; (2) medication access; (3) delivery of education; (4) clinician pre-commitment; and (5) EHR nudge. Each component will be rated by study staff using a scale of 0–3 (0 – not implemented; 1 – minimally implemented or implemented with low fidelity; 2 – mostly [but not completely] implemented or with minimal alternations affecting fidelity; 3 – fully implemented with high fidelity).

*Maintenance (secondary outcome*).

Maintenance will be defined as trends in discharge of PE patients following the completion of the 12-month post-implementation period.

### Effectiveness/Patient Safety (exploratory outcomes)

As well-implemented care pathways that discharge appropriate PE patients should be just as safe, if not safer, than care pathways that admit PE patients, effectiveness of the care pathway will be assessed through an examination of three patient safety outcomes, all assessed at 30 days post-discharge: (1) return to the ED, (2) any bleeding that leads to health care system interaction, and (3) all-cause death.

### Other measures

#### Organizational readiness for change

To assess baseline organizational difference in site readiness for change, we will also assess organizational readiness for change using the validated 20-item Organizational Readiness for Change Assessment (ORCA) during our pre-implementation meetings with the site clinical champions [21]. All three domains (evidence assessment, context assessment, and facilitation assessment) will be included this assessment.

### Data collection

In addition to the semi-structured interview data collected during the pre-implementation phase for Aim 1 analyses (described above), two other sources of data will be central to this evaluation. Clinical data and outcomes, including for our primary outcome of care pathway adoption, will be attained via the existing central MEDIC registry. Study staff reports will inform evaluations of implementation fidelity and organizational readiness for change.

### MEDIC registry data

Data collection for the majority of our implementation and clinical effectiveness outcomes will be obtained for analysis through the existing central MEDIC Data Registry. All MEDIC sites, including the 12 study sites, currently contribute electronically extracted data into this registry. This includes data from all ED visits with imaging ordered to evaluate for possible acute PE (primarily computed tomography [CT]). For our purposes, results of the CT scan along with ICD-10 diagnosis codes (I26) will be used to identify a cohort of patients with acute PE. Additional data collected for each case include key demographics, comorbidities, medications and other treatments administered, and disposition data (i.e., hospital admission, home discharge). These data undergo regular audits by the MEDIC team (distinct from our study team) to ensure data accuracy and completeness. Data on key outcomes will be available from the pre-implementation phase through the end of the maintenance phase (a minimum of three months after the 12-month post-implementation phase).

### Study team data

#### Organizational readiness for change

At baseline, study team members involved with the needs assessment will collectively complete an ORCA evaluation [21] on behalf of each site to assess differences in perceived organizational readiness for change. One study team member will provide an initial assessment and at least one additional team member will evaluate ratings for concordance and cross-site consistency in ratings. Disagreements in ratings will be brought to the full study team for final rating decisions.

### Implementation fidelity

Study team members will be trained in using the FRAME [18] and FRAME-IS [19] tools to report planned and ad-hoc modifications to care pathway components, as well as study-provided implementation support. Modifications will be tracked on both tools separately by site as appropriate throughout the pre-implementation, implementation, and post-implementation phases, with modifications queried with sites at least every three months.

Quantitative assessments of implementation fidelity will be assessed by study staff at three time points: (1) end of implementation period; (2) six months into the post-implementation period; and (3) at the end of the post-implementation period. While assessments at the end of the implementation period will be considered primary for purposes of analyses, later assessments allow for reporting of sites that may achieve full or high-fidelity implementation of key care pathway components after the end of the implementation phase; they also allow for a assessment of sites’ abilities to maintain care pathway components. Study team assessments will follow the same process as for the ORCA above, involving a minimum of two central study team members that are actively engaged in communication with sites as to implementation progress.

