### Centralized implementation support offered by the study team

To support our sites in implementing this new care pathway, we will also offer centralized implementation support, focused on scaling up training materials (high quality versions of which can be challenging/resource intensive to develop), helping site troubleshoot challenges that arise as they work through site-level implementation, and learning from other sites that are also actively implementing the care pathway. Strategy selection was informed by use of a modified implementation mapping approach [11], wherein data on barriers and facilitators was collected from our pilot site, change objectives related to these barriers were then identified, and a set of potential, appropriate implementation strategies were selected, each linked to one or more change objectives. From this set, we then selected an initial set of implementation strategies that addressed the most crucial barriers and were feasible. These strategies are described briefly below and full, initial specifications [12] are included in Fig. 2. Many of these strategies will utilize the sites’ existing clinical champions who currently collaborate with other clinical champions from across the state to implement evidence-based care strategies, such as reducing unnecessary imaging and reducing hospitalization for low-risk patients presenting with chest pain. Four strategies specifically are key to our team’s work:*Needs Assessment and Workflow Package Tailoring:* Study staff will conduct interviews with key site members to ascertain needs and then work with site members to tailor the care pathway to site capacity and capability.*Structured Provider Eduation Program:* We will offer all participating sites and their care provider teams educational sessions covering home management of low-risk PE. Content and delivery modality will be tailored to site needs and will be made available through various modalities, including in-person/virtual sessions and asynchronous materials. The Educational Program will cover the key elements of the pathway and the safety data underlying home management of PE. It will also include site-specific details about how to engage with the care pathway.*Building a Coalition to Support Implementation:* The study team will help the CQI champion identify and convene key stakeholders for implementing the care pathway at their site, including stakeholders related to establishing rapid follow-up and medication access, offering training opportunities for care teams, and implementing electronic health record (EHR) configuration.*Coaching for CQI Champion:* To help the CQI champion address barriers identified during the needs assessment and/or new barriers that emerge during the implementation process, study staff (including a clinical ED expert) will be available to meet with sites on a biweekly basis to talk about progress and help them strategize. This model of coaching is loosely based on models of External Facilitation that have proven successful for implementing other new care pathways [13–15].*Facilitating External Peer Support:* As an extension to site-specific activities, study staff will also work to facilitate communication between sites within a particular step to encourage peer support and information sharing, especially as it relates to addressing common or similar barriers.*Technical Assistance, including Support for EHR Builds*: We will offer sites the option to transfer the pilot site’s PESI calculator to their electronic health record system (if they also use Epic®) or will provide the underlying logic to facilitate the local build of a similar calculator and alert in other EHR systems.*Data Audit and Feedback:* Data on rates of discharge of low-risk PE patients will be provided to sites on a quarterly basis for purposes of monitoring progress through the existing MEDIC data registry.

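### Fidelity is scored by site-engaged staff and then reviewed by a second member, so as described there is no independent second rating from which to estimate inter-rater agreement

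*Protocol article*

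**What the plan says.** All references are to the protocol article.

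- **Who scores, and on what scale.** Under *Implementation Fidelity (secondary outcome)*: "Each component will be rated by study staff using a scale of 0–3". Five components are listed. The anchors are verbal grades of how completely and how faithfully each was put in place.
- **Relation of raters to sites.** Under *Implementation fidelity* (Study team data), rating is done by a process "involving a minimum of two central study team members that are actively engaged in communication with sites as to implementation progress". Study staff also coach: under *Centralized implementation support offered by the study team*, they "will be available to meet with sites on a biweekly basis to talk about progress and help them strategize".
- **Procedure.** "Study team assessments will follow the same process as for the ORCA above". The ORCA process, under *Organizational readiness for change* (Study team data), is: "One study team member will provide an initial assessment and at least one additional team member will evaluate ratings for concordance and cross-site consistency". Then: "Disagreements in ratings will be brought to the full study team for final rating decisions".
- **Timing.** Ratings are made at the end of implementation, six months into post-implementation and at the end of post-implementation. The first is named as primary for analyses. On the post-implementation phase, *Evaluation of implementation and effectiveness outcomes* says: "Sites will also begin to receive data audits from the study team during this time, showing their rates of PE discharge".
- **Use.** *Fidelity-informed Adoption* repeats the adoption analysis with the summed fidelity score added, as an exploratory analysis.

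**The concern.** A judgement-based score needs some evidence that a second person, working separately, would reach the same value. Here the second member starts from the first member's rating. Agreement reached that way mixes true reproducibility with deference to a score already on the page, and the two cannot be separated afterwards. Both members must also be in active contact with the site, so no rater stands outside the support effort.

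For the two later ratings there is a further exposure. The study team has by then sent the site its discharge rates, and the article describes nothing that keeps those figures from the raters. A site known to be discharging more patients could be scored more generously.

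At stake are the credibility of a named secondary outcome and the reading of the exploratory analysis that relates fidelity to adoption. The Discussion also presents the quantitative fidelity measure as one of two unique features of the study.

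**Working it through.** The plan states no agreement figure, so there is nothing to reproduce. The check sets the sections side by side, adds one count, and gives one illustration under stated assumptions.

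**1. Is there an independent second score?** An agreement statistic compares two scores, each formed without knowledge of the other. The process described is: initial score by member A; evaluation of A's score by member B; full team if they differ. B's view is formed after A's is known. The article does not say whether B records a score at all. Either way, no pair of independent scores results.

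**2. Which ratings follow the audits?** Table 1 gives audits monthly for six months and quarterly thereafter, while *Data Audit and Feedback* gives quarterly. The counts below are maxima, allowing the last audit to coincide with the rating.

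| Rating | Audits already sent, Table 1 schedule | Audits already sent, quarterly schedule |
|---|---|---|
| End of implementation (primary for analyses) | 0 | 0 |
| Six months post-implementation | up to 6 | up to 6/3 = 2 |
| End of post-implementation (12 months) | up to 6 + 6/3 = 8 | up to 12/3 = 4 |

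On either schedule, the first rating precedes the planned audits and the other two follow them.

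**3. Why agreement after review is not reliability (illustration only).** Weighted kappa is κ = 1 − Σw·o / Σw·e. Here o and e are the observed and chance-expected cell proportions, and w = ((i − j)/3)² on the 0–3 scale. Assumptions, none from the article: true levels spread evenly over the scale, rater error SD 0.7 scale points, 60 items treated as independent, 4,000 simulated sets. The share of items on which the second rater simply adopts the first score is varied.

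| Share adopted | Mean weighted kappa |
|---|---|
| 0% (independent) | 0.71 |
| 25% | 0.78 |
| 50% | 0.85 |
| 75% | 0.93 |

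The raters are equally reliable in every row; only the amount of copying changes. A high value from sequential review therefore cannot be read as reliability.

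**4. What independent scoring would give.** 12 sites × 5 components = 60 pairs per time point, and 60 × 3 = 180 over the three. Under the same assumptions, kappa from 60 independent pairs had a 95% simulation range of 0.57 to 0.82. The real pairs are clustered within 12 sites, so the true precision could be lower. The article elsewhere speaks of four components, which would give 12 × 4 = 48 pairs; that inconsistency is a separate matter.

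**The case against.** The strongest case for the plan has five parts.

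- **Safeguards exist.** There is a second evaluator, a cross-site consistency check and full-team adjudication. This stands: the process supports consistency. It does not measure reliability.
- **An article condenses.** Rater manuals, evidence lists and choice of agreement statistic may sit in a fuller document, and their absence here is no fault. This stands too. The point rests on what the article does fix: who rates, and that the second member works on the first member's ratings.
- **The team is not simply grading its own work.** A reader might infer that it is. Table 1 does not support that: the scored components are labelled as up to sites to offer and are led mainly by clinical champions and site IT staff. Study staff share only education delivery, and their coaching and coalition-building are not scored 0–3. What remains is that people who support a site may lean in its favour.
- **Knowledge of results need not manufacture a fidelity–adoption association.** A reader might infer that it would. The rating named as primary for analyses precedes the planned audits, and the later ratings have a stated descriptive purpose (late achievement and maintenance of components). They are not said to enter the adoption model. Any error rate for a false association would rest on invented shift sizes and on an analysis the article does not plan. A lean shared equally by all sites would also create no association.
- **Consequences are limited.** The primary outcome comes from registry data audited by a team separate from the study team, and the fidelity–adoption model is exploratory. This stands and limits the weight of the point.

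**Conclusion.** The point holds as an inexpensive improvement to a secondary process measure. It is not an error that threatens the trial's main result. As described, the procedure gives zero independent pairs of scores where 60 per time point are available from the same minimum of two raters. Inter-rater agreement cannot be estimated at any of the three time points, and scores may lean toward the first, site-engaged rater. In addition, the six-month and end-of-phase ratings could be influenced by known discharge rates; the end-of-implementation rating is not exposed through the planned audits.

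That scores are in fact inflated is not shown anywhere in the article, and no size can be put on it. The kappa values above illustrate a mechanism under assumed rater error and are not estimates for this trial. The conclusion assumes that the article states the rating procedure as it will be run. If a fuller document already has both raters score separately, the article's description should be reconciled with it.

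**What to change.** Change the two Study team data sections, *Organizational readiness for change* and *Implementation fidelity*, as follows.

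1. At each time point, the existing minimum of two raters each record all component scores independently, before seeing the other's.
2. They then compare scores and resolve differences by the existing full-team rule. The reconciled score is the one analysed.
3. Both raw scores are kept, and weighted kappa is reported for each time point.
4. Where team allocation allows, one rater is a member who does not coach that site and has not seen its discharge audits. Locking a rating before the current period's audit would not be enough, because earlier audits would already have been seen.
5. State under *Fidelity-informed Adoption* that the model uses the end-of-implementation rating and that the two later ratings are descriptive.

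The cost is a little more rater time, chiefly for a non-coaching rater to read the site record. Items 1 to 3 need no extra staff. Item 4 depends on team size and coaching allocation, which the article does not give, so it is conditional. The change has to precede the ratings it covers, since independent first scores cannot be recovered later.
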